## Methods/design

### Study design

The COBRA-PATH study is a prospective, single-center, randomized controlled trial. Patients will be randomized to ablation using a standard (noncontact force-sensing) catheter or ablation using a contact force-sensing catheter (Fig. 1). The follow-up period is 12 months from the index procedure. All operators in the electrophysiology center of Erasmus MC have significant experience in (P)SVT ablation (more than 200 PSVT ablations). The protocol follows the Standard Protocol Items: Recommendations for Interventional Trials (SPIRIT) 2013 Statement. The SPIRIT 2013 Checklist is provided in Additional file 1. Enrolment, intervention and assessment according to the time schedule of the study are presented in the SPIRIT figure in Additional file 2.

**Fig. 1 Fig1:**
[figure not shown]
Contact-Force-Sensing-Based Radiofrequency Catheter Ablation in Paroxysmal Supraventricular Tachycardias (COBRA-PATH) study flow chart. *Symptoms highly suggestive of PSVT: sudden onset of termination of rapid (and regular) palpitations. The palpitations can usually be terminated with the Valsalva maneuver or carotid massage. The patients have no evidence for an underlying structural heart disease. ^#^For a detailed explanation, see “Study population”. ^$^For a detailed explanation, see “Preprocedural preparation and electrophysiology (EP) study”. ^&^This follow-up can be scheduled any time during the 12-month follow-up period, in case the patient experiences recurrent symptoms (symptom-based follow-up). AE adverse event, AVNRT atrioventricular nodal re-entry tachycardia, CF contact force, FU follow-up, I/E inclusion/exclusion, PVST paroxysmal supraventricular tachycardia, SAE serious adverse event, WPW-AVRT Wolff–Parkinson–White syndrome–atrioventricular re-entrant tachycardia

### Study population

All patients without structural heart disease being referred to participating centers for standard electrophysiological study either because of pre-excitation detected on 12-lead surface ECG or because of palpitations associated with documented narrow-complex tachycardia (or clinical signs highly suggestive of the palpitation being associated with PSVT: sudden onset and termination of rapid and regular palpitations—the palpitations can usually be terminated with Valsalva maneuver or carotid sinus massage) will be eligible. In addition, in order to be eligible for participating in the trial, an electrophysiology study must identify AVNRT or WPW-AVRT (see clarification in the following) as the underlying arrhythmia mechanism [26–29]. In order to be included in the study, a subject must meet all of the following criteria:
Referral for electrophysiology study because of pre-excitation on 12-lead surface ECG and/or documented (or suspected) symptomatic PSVT: palpitations associated with narrow-complex tachycardia (≥ 1 episode) documented by a 12-lead electrogram, Holter monitoring, trans-telephonic event recorder, telemetry strip or implanted device (implantable loop recorder, pacemaker) within 12 months prior to referral to EPS; or frequent symptoms of palpitation (within 12 months prior to referral) associated with clinical signs highly suggestive of PSVT—sudden onset and termination of rapid (and regular) palpitations usually accompanied with neck pulsation and/or dizziness, termination with Valsalva maneuver or carotid sinus massage, and no evidence for an underlying structural heart diseaseIdentification of AVNRT or WPW-AVRT (with manifest or concealed accessory pathway) during standard EP studyVerbal consent to continue with ablation therapy after the diagnostic steps of the EPS identified the aforementioned arrhythmia mechanisms, and after the patient received sufficient information about the benefits and potential risks of the ablative treatment of the individual arrhythmia substrateInformed written consent to being included in the study

A potential subject who meets any of the following criteria will be excluded from participating in this study:
Evidence of structural heart disease and/or myocardial ischemiaPregnancy (and lack of exclusion of potential pregnancy)Age below 18 years

In this study protocol, we use the term WPW-AVRT to describe the following disease entities:
Patients with evidence of a manifest accessory pathway (i.e. pre-excitation on surface ECG and/or findings supporting anterograde conduction over an accessory pathway during standard EP study) who also present with documented narrow (or wide)-complex tachycardia, which proves to be orthodromic (or antidromic) AVRT by the EP study. (Note: antidromic AVRT is a quite rare entity.)Patients presenting with documented orthodromic AVRT using a concealed bypass tract (accessory pathway conducting only in the retrograde direction).Patients who possess a manifest accessory pathway (pre-excitation on ECG and/or evidence for anterograde conduction during EP study; similar to group 1) but have never experienced palpitations and have no prior documentation of tachycardia. In these patients, RF ablation of the accessory pathway will be offered for those individuals who possess a manifest accessory pathway with an anterograde ERP less than 240 ms, and/or for whom EP study identifies a reproducibly inducible AVRT. These patients can be enrolled in our study, even if no tachycardia had been experienced or documented in the past.

### Ethics

The study protocol was approved in September 2017 by the Medical Research Ethics Committee (2017-394) of Erasmus Medical Center in Rotterdam, the Netherlands. Patient inclusion began in June 2018 and is still ongoing. Written informed consent has and will be obtained from each participant.

### Primary and secondary outcome parameters

The primary outcome of this study is the number of radiofrequency ablations during the ablation procedures of AVNRT and WPW-AVRT. The secondary outcome parameters are overall duration of radiofrequency applications, acute procedural success/failure, fluoroscopy time, total procedural duration, (serious) adverse events and long-term procedural success. The following additional characteristics and parameters are collected and investigated during the study: baseline demographic characteristics of patients, previous antiarrhythmic drug treatment, history of cardiac arrhythmias (first onset of PSVT, and other possible associated arrhythmias, e.g. atrial fibrillation, atrial flutter, premature ventricular contraction, (non)-sustained VT) and prior ablation history.

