**Discussion:**

We expect to see a reduced number/duration of RF applications required to achieve effective lesion creation, and consequently a decrease in total procedure/fluoroscopy times. Although a significant improvement in procedural success rates (acute/long term) might not be feasible to demonstrate (given the relatively high success rate of the standard ablation method), the possible decrease in procedure duration and the consequential reduction of radiation exposure has important clinical implications for both operators and patients undergoing the procedure.

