### Study groups and randomization process

Consecutive patients on the waiting/referral list for PSVT ablations (referred to our tertiary center by other hospitals) will be screened for eligibility by dedicated study coordinators. When they meet the inclusion criteria, the patients will be enrolled in the study (as depicted in the flowchart for the study; see Fig. 1). After enrolment, patients will be allocated a unique study subject number in chronologically ascending order. Subsequently, they will be randomized to two treatment arms: the “CF-sensing” arm, ablation with a CF-sensing ablation catheter; and the “conventional” arm, standard ablation approach using a conventional (noncontact force-sensing) ablation catheter. Randomization will be performed by a computer-generated program (ALEA) based on a block randomization protocol using a block size factor of four. Randomization into the two treatment arms will be carried out with a 1:1 randomization ratio (50% probability for both treatment arms). The process of randomization will follow the general concepts of allocation concealment by incorporating the following prerequisites into the conduct of randomization: the EP specialists performing the ablation procedures do not have knowledge on the method of randomization utilized in the study; the EP specialists performing the ablation procedures do not keep a record of the results of randomization during previous ablation procedures; withdrawal from enrolment and randomization after the initial screening process and the subsequent EP study (that was positive for AVNRT or WPW-AVRT) must be explained thoroughly in the official clinical report by the treating specialist; the person in charge of the randomization process will not be the treating physician and neither will he/she be involved in the patient selection process; and the person in charge of the randomization will be contacted (over the telephone) by the treating specialist after the diagnostic part of the procedure has been completed. Stratification for study specific factors will not be conducted. The study will be performed in an open-label fashion: neither the patient nor the electrophysiologist (performing the procedure) will be blinded for the specific type of procedure.

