### Electrophysiology procedure and catheter ablation

#### Preprocedural preparation and electrophysiology (EP) study

The procedures are performed under local anesthesia. In the case of a patient on anticoagulation therapy, this is decreased/discontinued before the procedure according to local guidelines. Antiarrhythmic medication is stopped 5 days before the procedure. The diagnostic EP study is implemented according to standard protocols for diagnosing SVTs: vascular access is created with femoral venous puncture and multipolar diagnostic catheters are placed in standard locations within the cardiac chambers: the coronary sinus, the right ventricle and the region of the bundle of His. Intravenous heparin is used during the procedure for anticoagulation (guided by the activated clotting time when necessary). Standard pacing maneuvers (atrial/ventricular extrastimulus testing, atrial/ventricular incremental pacing and specific pacing maneuvers to assess accessory pathway conduction and to induce and analyze SVTs) are performed to confirm the diagnosis of AVNRT or WPW-AVRT. After confirming the diagnosis of AVNRT/WPW-AVRT, the operator informs the patients about the specific diagnosis and briefly describes the expected success rates and safety concerns regarding the ablation of the particular subtype of arrhythmia substrate. Next, in order to continue with ablation, verbal consent is obtained from the patient (see protocol flowchart in Fig. 1).

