#### Mapping and ablation of the underlying arrhythmia substrate

In the case of a left-sided ablation, the choice of access to the left atrium/ventricle (retrograde via the femoral artery vs. a transseptal approach) is left to the discretion of the operator. Transseptal punctures are guided by intracardiac echocardiography (ICE).

Depending on the results of the randomization, the subsequent steps of mapping/ablation are performed using either a conventional (nonirrigated, non-CF-sensing) manual RF ablation catheter (conventional arm) or the TactiCath Quartz open-irrigated contact force-sensing catheter (CF-sensing arm). Stable catheter–tissue contact (minimum of 10 s in duration) with a minimum CF exceeding 5–10 g (and an optimal CF within the range of 15–20 g) is targeted in the CF-sensing group. The TactiCath catheter is used in a virtual “nonirrigated mode” (saline flow set to ~ 1 ml/min) to achieve a similar degree of temperature control as in the case of conventional nonirrigated catheters. In both groups, the power (usually between 15 and 55 W) and the duration (usually between 60 and 90 s) settings of individual RF applications will follow local laboratory standards and will be left at the operator’s discretion. The ablation procedures are continued until the clinical tachycardia is no longer inducible and/or the conduction through an accessory pathway is terminated, provided that these clinical endpoints can be achieved with acceptable clinical risk–benefit ratios (e.g. no signs of imminent complete AV-block, no signs of pericardial effusion, etc.). Thereafter, the inducibility of the clinical tachycardia and/or conduction over an accessory pathway is reassessed throughout a waiting time of 30 min from the last RF application. No additional applications are implemented until further programmed stimulation shows evidence for recurrence of inducibility and/or re-conduction over an accessory pathway.

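### Procedure duration, and probably fluoroscopy time, count time spent before randomisation, which costs precision in two secondary outcomes

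*Protocol article*

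**What the plan says.** The Protocol article, under Primary and secondary outcome parameters, lists among the secondary outcomes "overall duration of radiofrequency applications, acute procedural success/failure, fluoroscopy time, total procedural duration". No start or stop point is given for either time. Under Statistical analysis, both are compared between arms by a two-sample t test or a Mann–Whitney test.

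Under Study groups and randomization process, the person in charge of randomisation "will be contacted (over the telephone) by the treating specialist after the diagnostic part of the procedure has been completed". The section on the EP study shows what comes before that call: "vascular access is created with femoral venous puncture and multipolar diagnostic catheters are placed in standard locations within the cardiac chambers", then the pacing manoeuvres, the explanation of the diagnosis and verbal consent. The arms separate only in the next section: "Depending on the results of the randomization, the subsequent steps of mapping/ablation are performed using either a conventional" catheter or the contact-force catheter. After ablation, inducibility or pathway conduction "is reassessed throughout a waiting time of 30 min from the last RF application".

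The Discussion part of the abstract expects fewer or shorter applications and "consequently a decrease in total procedure/fluoroscopy times". It adds that better success rates may not be demonstrable, and that shorter procedures with less radiation would matter clinically.

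**The concern.** Time that has elapsed before allocation cannot be a treatment effect. If it is counted in the outcome, it contributes the same expected amount to both arms and its own patient-to-patient variation to the standard error. That variation may be considerable: the trial mixes AVNRT with manifest, concealed and asymptomatic accessory pathways, and randomisation is not stratified.

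These are secondary outcomes, but the abstract rests its clinical message on them. A less precise comparison makes a real shortening easier to miss and makes any shortening look smaller in percentage terms.

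**Working it through.** **1. Order of events against what is measured.**
- Before the call: femoral access, diagnostic catheters, pacing and induction, explanation and verbal consent.
- After the call: mapping, ablation, and the wait after the last application.
- Measured: total procedural duration and fluoroscopy time.

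The randomisation section itself describes the diagnostic study as a part of the procedure, so a total that starts with the procedure includes it. For fluoroscopy the only support is the abstract's joint reference to total procedure and fluoroscopy times.

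**2. The plan's own figure.** The sample size uses log application counts: difference 1.39 − 1.043 = 0.347, SD 0.59, power 80%, two-sided 5%. Then n = 2 × (1.96 + 0.84)² × (0.59/0.347)² ≈ 45.3, so 46 per arm, as stated. This concerns the number of applications. The article gives no mean, SD or power for procedure duration or fluoroscopy time, so everything below about phase times is assumed.

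**3. Effect on the standard error.** For independent phases, SD(total)² = SD(before)² + SD(after)². If the phase before randomisation carries a share s of the variance, dropping it multiplies the standard error by √(1 − s):
- s = 25%: √0.75 = 0.866, a cut of about 13%.
- s = 50%: √0.50 = 0.707, a cut of about 29%.

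**4. Illustration in power.** Power = Φ(δ / (SD × √(2/n)) − 1.96) with n = 46 per arm. Assume 60 min (SD 30) after randomisation, shortened by 25%, so δ = 15 min.

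| Diagnostic phase counted | SD of counted time | Power | Relative reduction |
|---|---|---|---|
| none | 30.0 | 67% | 15/60 = 25% |
| 30 min (SD 10) | 31.6 | 62% | 15/90 = 17% |
| 45 min (SD 20) | 36.1 | 51% | 15/105 = 14% |
| 60 min (SD 30) | 42.4 | 40% | 15/120 = 12.5% |

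With 40 min (SD 25) after randomisation and δ = 10 min, 48% falls to 43%, 32% and 23%. Across both cases the loss is about 5 to 27 points.

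**5. The 30-minute wait.** A constant added to every patient leaves the difference in minutes, the SD and the ranks unchanged, so power is unchanged. Only the percentage moves: in the 45-minute row, from 15/105 = 14% to 15/135 = 11%.

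**6. Size of the expected saving.** From the article's figures, 0.25 × 4.81 = 1.2 applications. At 60–90 s each that is 1.2–1.8 min of RF time. Adding an assumed 1–3 min of remapping per application gives 1.2 × 2 = 2.4 min to 1.2 × 4.5 = 5.4 min. With 56 per arm (112 in all), the difference detectable at 80% power is 2.80 × √(2/56) = 0.53 SD: about 16–32 min for an assumed SD of 30–60 min. Applying the 13% to 29% cut from step 3 brings this to about 11–28 min.

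**The case against.** **Definitions may lie elsewhere.** A condensed article can leave start and stop points to the full protocol, which is not shown. This stands in part. Inclusion of the diagnostic phase is the natural reading of a total, not an explicit statement, and it is weaker for fluoroscopy. But the article itself sets a total beside randomisation in mid-procedure, and those two fit badly.

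**Whole-procedure time is a legitimate outcome.** Patients and operators bear the whole duration and the whole radiation exposure, and the atrial fibrillation studies the article relies on are cited for total procedure time. This stands as a reason to keep reporting totals. It does not make them the more sensitive comparison of the catheters.

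**The gain may be too small to matter.** On step 6, even the improved detectable difference is at least twice the largest estimated saving. This stands as a limit on what the change can achieve. The estimate counts only fewer applications, however. The article's Discussion also expects less time spent assessing signal or impedance drop, so the true saving could be larger.

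Three stronger readings are tempting and are not supported:
- A reader might infer that the closing wait hides the effect. Step 5 shows that it does not. The wait is also not wholly beyond the catheter's influence: it runs from the last application, so early recurrence that prompts more RF restarts it.
- A reader might infer that chance imbalance in the diagnostic phase would pass for a treatment effect. That variation is already in the observed SD and hence in the standard error, so false positives stay at 5%.
- A reader might infer that any reduction is bound to be swamped. That depends on SDs the documents do not give.

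**Conclusion.** The point holds as a matter of precision. Total procedural duration, on its natural reading, includes time before allocation; fluoroscopy time probably does too. The comparison is unbiased and its error rate is intact. What is lost is precision and part of the relative effect: the standard error would fall by about 13% to 29% if the diagnostic phase carries 25% to 50% of the variance.

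That range assumes independent phases. Positive correlation between them would make the total more variable still; a sufficiently negative one could remove the gain. The power figures rest on assumed phase times and show direction and rough scale only.

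The primary outcome and the sample size are untouched. Nothing here shows that the trial could detect a saving of a few minutes, before or after the change.

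**What to change.** State the start and stop points of both times. At the randomisation telephone call, which already takes place, record the clock time and the cumulative fluoroscopy time. Compare procedure time and fluoroscopy time from randomisation onward between arms, or analyse the totals with the pre-randomisation portion as a covariate. Waits restarted by recurrence stay in the window, since the catheter may affect them. Continue to report whole-procedure totals.

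If the full protocol already starts the clock at or after randomisation, it is enough to say so.

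The cost is two readings per patient and a dated change of outcome wording. Because the trial is open-label and already recruiting, the change should be made without sight of results by arm. For patients already treated, the clock time may be recoverable from the procedure log or the randomisation system, but the fluoroscopy reading may not be. The number of patients without it should be reported, and the whole-procedure fluoroscopy total remains available for everyone.

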### Study groups and randomization process

Consecutive patients on the waiting/referral list for PSVT ablations (referred to our tertiary center by other hospitals) will be screened for eligibility by dedicated study coordinators. When they meet the inclusion criteria, the patients will be enrolled in the study (as depicted in the flowchart for the study; see Fig. 1). After enrolment, patients will be allocated a unique study subject number in chronologically ascending order. Subsequently, they will be randomized to two treatment arms: the “CF-sensing” arm, ablation with a CF-sensing ablation catheter; and the “conventional” arm, standard ablation approach using a conventional (noncontact force-sensing) ablation catheter. Randomization will be performed by a computer-generated program (ALEA) based on a block randomization protocol using a block size factor of four. Randomization into the two treatment arms will be carried out with a 1:1 randomization ratio (50% probability for both treatment arms). The process of randomization will follow the general concepts of allocation concealment by incorporating the following prerequisites into the conduct of randomization: the EP specialists performing the ablation procedures do not have knowledge on the method of randomization utilized in the study; the EP specialists performing the ablation procedures do not keep a record of the results of randomization during previous ablation procedures; withdrawal from enrolment and randomization after the initial screening process and the subsequent EP study (that was positive for AVNRT or WPW-AVRT) must be explained thoroughly in the official clinical report by the treating specialist; the person in charge of the randomization process will not be the treating physician and neither will he/she be involved in the patient selection process; and the person in charge of the randomization will be contacted (over the telephone) by the treating specialist after the diagnostic part of the procedure has been completed. Stratification for study specific factors will not be conducted. The study will be performed in an open-label fashion: neither the patient nor the electrophysiologist (performing the procedure) will be blinded for the specific type of procedure.

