## Trial status

Recruitment of participants started on 25 August 2017 and is expected to be completed on 30 June 2020. This manuscript is based on protocol version 02 of 25 August 2017.

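### The article prints the block size of four while inclusion is open, so operators' ignorance of the method can no longer be relied on as a concealment safeguard

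*Protocol article*

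**What the plan says.** All of the following is in the protocol article.

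- **Sequence.** Under Study groups and randomization process, a computer program (ALEA) allocates 1:1 "based on a block randomization protocol using a block size factor of four". The same section adds: "Stratification for study specific factors will not be conducted".
- **Setting.** Study design states: "The COBRA-PATH study is a prospective, single-center, randomized controlled trial". On blinding, "neither the patient nor the electrophysiologist (performing the procedure) will be blinded for the specific type of procedure".
- **Concealment.** The same section lists several prerequisites. The first is that "the EP specialists performing the ablation procedures do not have knowledge on the method of randomization utilized in the study". The second is that these specialists "do not keep a record of the results of randomization during previous ablation procedures". The others are that a withdrawal after a positive electrophysiology study must be explained in the clinical report, that the person who randomizes neither treats nor selects patients, and that the treating specialist telephones that person once the diagnostic part is finished.
- **Timing.** The Ethics section describes inclusion as still under way. Trial status says that recruitment "is expected to be completed on 30 June 2020".

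**The concern.** The first safeguard and the published text cannot both stand. A single section relies on operators not knowing the method and also sets out that method, down to the block size, while patients are still being entered. The second safeguard covers written records only, and an operator can remember recent cases without one.

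The order of events is what makes this matter. The treating specialist knows the arrhythmia substrate before placing the randomization call, and the plan foresees that a patient may be withdrawn at that point. The Discussion says that some locations, such as the right free wall, are harder to ablate. Difficulty plausibly drives the number of RF applications, which is the primary outcome. If an operator anticipated the next arm and held back a hard case, the arms would differ in case mix on the factor that drives the endpoint. The analysis could not reliably repair that.

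**Working it through.** The article gives no predictability figure to reproduce. Its total of 112 is used below only as a multiplier, and its stated steps do lead there: 92 × 1.15 = 105.8, about 106; 106 / 0.95 = 111.6, rounded up to 112.

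**Inputs from the article:** block size 4 (one size given, no variation mentioned), ratio 1:1, one stream, one center, operator unblinded, 112 patients.

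**1. Allocations that are certain under blocks of four.** There are six equally likely orders of two A and two B. An allocation is certain once one arm is used up in the block.

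- Positions 1 and 2: never certain.
- Position 3: certain if the first two match, which holds in 2 of 6 orders, so 1/3.
- Position 4: always certain.

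Share = (0 + 0 + 1/3 + 1) / 4 = 1/3. In 112 patients (28 blocks) this is 112 / 3 = 37.3, about 37. It applies to an observer who knows the block size, where each block starts and every earlier allocation.

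**2. Best-guess accuracy for the same observer.** Guess the arm with more places left, and toss a coin when they are level.

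- Position 1: 1/2.
- Position 2: 2/3.
- Position 3: 1/3 × 1 + 2/3 × 1/2 = 2/3.
- Position 4: 1.

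The sum is 17/6 of 4, so accuracy is 17/24 = 70.8%, against 50% under simple randomization.

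**3. Partial knowledge.** Study design speaks of operators in the plural but gives no number. Assume that the operator knows the position in the block and sees each earlier allocation independently with probability q. Certainty then requires that both earlier allocations of the exhausted arm were seen, which has probability q². The share becomes (1/3 × q² + q²) / 4 = q²/3.

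| Assumed q | Share certain | Of 112 |
|---|---|---|
| 1 | 33.3% | 37.3 |
| 1/2 | 8.3% | 9.3 |
| 1/3 | 3.7% | 4.1 |
| 1/4 | 2.1% | 2.3 |

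**4. Randomly varying blocks.** This was simulated with 400 sequences of 112 and block sizes drawn with equal probability. The observer knows the set of possible sizes and all earlier allocations and updates on them.

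| Block sizes | Certain | Best guess correct |
|---|---|---|
| 4 only | 33.3% | 70.8% |
| 4, 6 | 5.4% | 69.3% |
| 2, 4, 6 | 4.1% | 70.1% |
| 4, 6, 8 | 2.0% | 68.0% |

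The gain is in certainty. Best-guess accuracy hardly moves.

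**The case against.** The strongest reply is that much of the concealment scheme survives. Allocation comes by telephone from someone who neither treats nor selects patients, consecutive patients are screened by coordinators, and a withdrawal after a positive study must be explained in the clinical report. That duty directly deters the behavior feared here. This stands: these measures reduce the risk. But they hide the list and document withdrawals; they do not prevent an inference from a known block size and remembered allocations. A reader might infer that concealment as a whole is defeated, and the article does not support that.

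A reader might also infer that a third of this trial's allocations are in fact predictable. That is the maximum, for a fully informed observer. The article says that the operator performing a procedure is unblinded; it does not say that colleagues see each other's allocations.

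A third tempting reading is that operators could use a prediction to steer a difficult case to another type of catheter under the section on exclusion of enrolled patients from further follow-up. Those rules apply to patients already randomized, when the arm is known. Prediction plays no part there and varied blocks would not change it. Only withdrawal before the call depends on prediction.

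Finally, that the block size is fixed is inferred from the single size given, and the text has no publication date. Both inferences are the natural reading, but the number of allocations still to come at publication cannot be determined.

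**Conclusion.** The point holds as a conflict within the plan and a risk of selection bias. The safeguard of operators not knowing the method cannot be relied on once the article prints it during recruitment, and the rule on records leaves memory uncovered. At most 1/3 of allocations (about 37 of 112) would be predictable with certainty, falling to about 8% to 2% if each earlier allocation is seen with an assumed probability of 1/2 to 1/4. The maximum assumes that the block size is always four and that block starts and all earlier allocations are known.

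Nothing in the article shows that anyone predicted an allocation or withdrew a patient for that reason, so the size of any bias is unknown. The sample size is not affected. This is an improvement that should be made, and it does not by itself invalidate the design.

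**What to change.** For the remaining allocations, set ALEA to randomly varying block sizes, for example 4, 6 and 8. The randomization office should hold the sizes and not disclose them until recruitment closes. Replace the statement of a block size of four accordingly, and make the switch at the end of a completed block. This cuts certain predictions to about 2% even for an observer who knows the possible sizes. It should not be presented as removing guessing, since best-guess accuracy remains about 68%.

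For patients already randomized, add a sensitivity analysis of the primary endpoint that excludes allocations that were deterministic under the blocks of four: every fourth position, and the third where the first two matched. The allocation list identifies them. If all 112 had been allocated in blocks of four, about 37 would be dropped and about 75 kept, so precision falls. The analysis also keeps second positions, which an informed guess gets right 2/3 of the time, so it is a check and not a correction.

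The cost is a system setting, a short amendment, and a maximum end-of-trial imbalance of 4 patients instead of 2 (half the largest block).
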